### Statistical analysis

Due to the correlation between the reminders for the same patient, the patients assigned to the same professional, and the professionals at the same centre, hierarchical modelling will be used, allowing simultaneous estimation of a factor effect at various levels.

### Resolution of the reminder

To estimate the effect of the intervention on improving the resolution of each reminder, a two-level analytical strategy will be used:Professional/PCC levelThe effect of the quality variables—EQA, EQR, and EQPF—on the resolution of the reminder will be evaluated at the aggregate level: percentage of reminders resolved. The Pearson correlation coefficient and scatter plots will be used for this purpose.Reminder levelHierarchical or multilevel methods will be used to take into account the structure of the information and be able to introduce variables from different levels as adjustment variables in estimating the intervention effect. Multilevel logistic regression models will be fitted. The analytical strategy will be to estimate the intervention effect, taking into consideration the randomized professionals; next, the effect size will be estimated by introducing the quality variables from the professional level (EQPF, EQA, and EQR). Finally, we will determine whether introducing variables from the reminder level changes the intervention effect. A subgroup analysis will also be done, by type of reminder.

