## Background

Computerization of medical records and the availability of computer access in all medical offices in the primary care setting have made it possible to study the impact of this computerization in daily clinical practice (Fina et al. 2006). The Catalan Institute of Health (*Institut Català de la Salut*, ICS) is the main public provider of primary care services in the National Health System of Catalonia, with 282 primary care teams serving nearly 6 million people (80 % of the Catalan population). The 8000 health professionals comprising these teams provide family, paediatric, and nursing care. Since 2005, all ICS primary care providers have used the same electronic health records system, called ECAP, and since 2006 have been able to access a feedback system, updated monthly, that reports on quality indicators evaluating the care provided. All professionals have access to their rates of adherence to the evaluation standards and can view detailed information at the patient level. The feedback system also compiles a list of patients who do not meet all established criteria of the 62 evidence-based recommendations that constitute a unique index known as the Quality of Care Standard (*Estàndard de Qualitat Assistencial*, EQA). At present, health professionals have point-of-care access to all of these results, with no additional data-recording effort on their part (Coma et al. 2013).

Primary health care allows longitudinal follow-up of a population. It also requires attention to multiple health conditions and disease prevention activities in a relatively brief office visit. Bodenheimer estimated that a primary care physician would require 18 h per workday to implement all of the prevention activities recommended by experts in chronic diseases (Bodenheimer 2008). Given the multitude of recommendations, it would be of great interest to health care professionals to have tools available that would help them carry out evidence-based activities. One of the strategies used to improve clinical practice is the incorporation of recommended activities as reminders in the clinical record (Jamtvedt et al. 2003).

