The availability of the shared electronic health record allows electronic reminders at the point of care, which has been associated with an improvement in clinical practice, estimated at 4.2 % (interquartile range 0.8–18.8 %). This wide variability could be explained by differences in the settings where the studies were carried out, the basal levels of adherence, or the characteristics of the reminders studied (Shojania et al. 2010).

Most of the randomized clinical trials that have evaluated the effectiveness of reminders in the primary care setting have included reminders for just one disease or clinical condition (Eccles et al. 2002; Filippi et al. 2003; Flottorp et al. 2002; Hicks et al. 2008; Krall et al. 2004; Safran et al. 1995; Sequist et al. 2005; Tierney et al. 2003; van Wyk et al. 2008). The studies that have included interventions with multiple reminders have focussed on preventive measures such as vaccinations and screenings or potential adverse effects of medications (Frank et al. 2004; Tamblyn et al. 2003).

In a retrospective analysis, an association was observed between the level of adherence to the recommendations of interest and the frequency of accessing the feedback provided and the patient list. In other words, the professionals who consulted their own quality results and the status of their patient lists showed greater improvement in their clinical indicators than their colleagues who did not consult the feedback results; in addition, a temporal relationship was detected between the availability of feedback and the clinical improvement (Fina et al. 2006). Even though different clinical trials have studied the impact of paper reminders and other interventions such as economic incentive or educational support materials, there is a lack of scientific evidence on the impact of computerized reminders (Shojania et al. 2010).

In 2012, a maximum of 10 computerized reminders per patient was introduced into the ECAP system, visible to the health professional during the patient visit and related to 25 of the 62 recommendations considered as quality indicators in the EQA. We designed a clinical trial to evaluate whether adding computerized reminders to a well-established feedback system would improve adherence to multiple clinical recommendations in the primary care setting.

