#### Control group

During the clinical trial, all study participants, including those in the control group, will continue to receive the usual feedback established in 2006. This feedback consists of a monthly update for each family physician and primary care nurse of their percentage of adherence to each of the evidence-based recommendations in the EQA, along with a comparison of the month’s results with their own basal data, with the rest of their team, and with the mean of all ICS teams.

For ease of interpretation, the results will be color-coded by target values. For 20 of the 25 recommendations, in addition to the numerical score, professionals will be able to consult the list of patients who do not meet the target; the goal is that the professional will review and take action with those individuals. Access to the feedback screen is provided as a direct link within the electronic health record (Figs. 1, 2, in Catalan; an online demonstration of this feedback system is available at: http://www.amf-semfyc.com/sisap/) (Coma et al. 2013). The monthly results are also used as part of a performance incentive variable in the compensation model; during the intervention year, the incentive will not exceed a total of 750 euros per physician and 380 euros per nurse.

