#### Randomization

The PCC will be the unit of analysis, so that all professionals from the same centre will be assigned to the same arm of the trial. Randomization will be done with the Stata/SE (v. 11.2, StataCorp) module for the design of randomized clinical trials (Ryan 1990). With the goal of achieving a balanced distribution of the quality of care by PCC in each arm, centres will be stratified by the quintiles of EQA results in the month prior to study initiation. The procedure will consist of obtaining the ICS list of PCCs, importing the data in STAT format, applying the inclusion and exclusion criteria, and adding the EQA value for each PCC. The PCCs will be allocated in randomized blocks of 6, 12, and 18 to achieve the same number of PCCs in each of the study groups (Fig. 3).

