Percentage of assigned population visiting the PCC previous year	Percentage of the assigned population who visited the PCC/individual health professional during the year prior to the study. A priori, professionals who see a larger percentage of their assigned patients have more opportunities for interventions to improve clinical situations.
Frequency of patient visits	Number of visits per year/population with at least one visit in the previous year. A priori, a greater number of patient contacts with a health professional will yield more opportunities to correct clinical situations.
EQA	Synthetic clinical indicator consisting of a group of indicators based on scientific evidence.
EQPF	Synthetic indicator developed by the ICS Department of Medication Strategy, including 21 indicators related to the quality of the prescription
EQR	Synthetic indicator that analyses the difference between population prevalence and a patient cohort, which identifies professionals with a good level of recording quality

*EQA* quality care indicator, *EQPF* prescription quality indicator, *EQR* quality of data recording, *CRG* clinical related groups, *PCC* primary care centre

^a^Anonymized data from patient records

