### Time to resolution of the improvable clinical situation

Time to resolution will be estimated by the Kaplan–Meier method and comparisons will be done using the log-rank test. Multilevel survival analysis will be used to homogenize the data structure (Yau 2001). The analytical strategy is the same as described above: an initial model will be adjusted to estimate the intervention effect, introduce the professional-level variables (EQA, EQR, EQPF), and then determine whether the variables at the reminder level change the estimated intervention effect.

The level of significance will be established at 5 %. All analysis will be done using the Stata/SE software, version 11.2 (StataCorp 2012).

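### The models use only composite quality scores, and only from the second step on, although pre-trial adherence on each recommendation is already held; adjusting for it would add precision at little cost.

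*Protocol article*

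**What the plan says.** **Models.** The Protocol article, under Resolution of the reminder, describes three steps. The first is "The analytical strategy will be to estimate the intervention effect, taking into consideration the randomized professionals", with no baseline covariate named. In the second, "the effect size will be estimated by introducing the quality variables from the professional level (EQPF, EQA, and EQR"). The third adds reminder-level variables. Under Time to resolution, the survival models follow the same order: an initial model, then "introduce the professional-level variables (EQA, EQR, EQPF").

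**Variable list.** Table 3 describes EQA as "Synthetic clinical indicator consisting of a group of indicators based on scientific evidence". It lists EQPF (prescription quality) and EQR (recording quality) beside it. It has no entry for pre-trial adherence on a single recommendation, and gives no date for EQA, EQPF or EQR.

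**Design.** Under Randomization, "centres will be stratified by the quintiles of EQA results in the month prior to study initiation". The Background describes EQA as built from "62 evidence-based recommendations that constitute a unique index known as the Quality of Care Standard", and the reminders as "related to 25 of the 62 recommendations considered as quality indicators in the EQA".

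**Data already held.** Under Control group, the monthly feedback, which runs in every arm, gives each physician and nurse "their percentage of adherence to each of the evidence-based recommendations in the EQA" and compares it with that professional's own baseline.

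**The concern.** In a cluster trial with many observations per centre, the width of the confidence interval is set mainly by how much centres differ. The number of centres is fixed here, and further reminders add almost nothing. A baseline covariate that predicts a centre's later result is one of the few ways left to narrow the interval.

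EQA is a diluted version of such a covariate. Of its 62 recommendations, 62 − 25 = 37 have no reminder. From Table 1, blood pressure and smoking make up (534,702 + 711,392) / 1,620,643 = 77% of expected reminders, so two recommendations dominate any pooled result. For the planned analyses by type of reminder, a broad index is further still from the outcome. The more specific value sits in the sponsor's monthly file and is not used.

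At stake is the ability to detect an effect below the 10-point target. The Background cites 4.2% as the typical improvement with point-of-care reminders, and the Discussion says that adding reminders to established feedback may give a smaller effect.

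**Working it through.** **1. The plan's own figure.** Sample size gives 15,950 reminders per group. Comparing 59% with 49% at two-sided alpha 0.01 and 95% power, the usual two-proportion formula gives:

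(2.576 × √(2 × 0.54 × 0.46) + 1.645 × √(0.59 × 0.41 + 0.49 × 0.51))² / 0.10² ≈ 882 per group

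With 10% loss this is 882 / 0.9 = 980. The stated number then implies a design effect of 15,950 / 980 = 16.3, or about 1 + 15.3 / 0.05 ≈ 306 reminders per centre. The article states no cluster size, so the figure is neither reproduced nor shown to be wrong. This point does not depend on it.

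**2. Inputs.**
- ICC ρ = 0.05 (Sample size).
- Centres: 282 less 2 pilot teams, in 4 equal groups, so k = 70 per arm. Other exclusions would lower this.
- Reminders per centre: Table 1 total 1,620,643 / 282, so m ≈ 5,747. At the stated sample size after loss, m = 15,950 × 0.9 / 70 ≈ 205.
- Proportions: 59% in the intervention arm, and 59% less the effect in control.
- Effect: 4.2%, read as percentage points.
- Alpha 0.05 (the stated significance level).
- r, the centre-level correlation of the pre-trial value with later resolution: not in the documents, **assumed** 0.3 to 0.7.

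**3. Share of variance between centres.** ρ / (ρ + (1 − ρ)/m) is 99.7% at m = 5,747 and 92% at m = 205.

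**4. Gain against no covariate.**

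SE² = [p₁(1 − p₁) + p₀(1 − p₀)] × [ρ(1 − r²) + (1 − ρ)/m] / k

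With p₁ = 0.59 and p₀ = 0.548, the first bracket is 0.2419 + 0.2477 = 0.4896. At r = 0, SE = √(0.4896 × 0.05017 / 70) = 0.0187. Power = Φ(0.042/SE − 1.96).

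| assumed r | SE (points) | reduction | power for 4.2 points at 5% |
|---|---|---|---|
| 0 | 1.87 | – | 61.1% |
| 0.3 | 1.79 | 4.6% | 65.2% |
| 0.5 | 1.62 | 13.3% | 73.5% |
| 0.7 | 1.34 | 28.5% | 88.0% |

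**5. Gain beyond EQA.** The second-step model already contains EQA, so the fair comparison there is with a model that explains part of the variation. If the multiple correlation rises from an assumed 0.5 to 0.6, the SE ratio is √(0.64/0.75) = 0.92, a reduction of about 8%. If it rises to 0.7, the ratio is √(0.51/0.75) = 0.82, about 18%.

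**6. Rare reminder types.** For ACEI/ARB treatment, 11,394 / 282 ≈ 40 reminders per centre, and the between-centre share is 68%. Using the same formula and proportions, the SE falls from 2.27 to 2.07 points (9%) at r = 0.5 and to 1.85 (18%) at r = 0.7.

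**7. The 10-point target.** With p₀ = 0.49 and no covariate, SE = 0.0188 and power at alpha 0.01 is Φ(0.10/0.0188 − 2.576) = 99.7%. At m = 205 it is 99.4%.

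**The case against.** The strongest case against is that this is an optional refinement of a design that already uses pre-trial quality and has ample power for its stated target.

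- **Pre-trial quality is used.** Prior-month EQA, which covers the reminder recommendations, stratifies the randomisation, and EQA enters the second model. A reader might infer that no pre-trial information on the outcome is used; the documents contradict that. Stratification also limits chance imbalance. This stands.
- **The gain is unknown.** No correlation is given. Table 3 also lists other centre-level variables (socioeconomic index, rurality, visit frequency) that may explain part of the variation. The step 4 figures are therefore an upper comparison, and step 5 is closer to the real increment in the second model. This stands.
- **Adherence is a proxy.** The feedback value is the share of patients who meet a recommendation. The outcome is resolution of reminders that all start unresolved. A centre with high adherence may be left with harder cases, so even the sign of r is uncertain. This stands and favours a prior-year resolution rate. A fixed covariate does not need a known sign, however, and a weak one costs almost nothing with about 70 centres per arm.
- **Covariate choice belongs in an analysis plan.** Detail often does. Here the article itself names the covariates, their order and a variable list, so the choice can be commented on.

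A reader might also infer that the undated EQA in the second step is measured during the trial, so that the model adjusts away part of the effect. The article gives no date, so this is not established; fixing the date removes the doubt.

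**Conclusion.** The point holds as lost efficiency. It is neither an error nor a source of bias, and the trial is not underpowered for the difference it calls clinically relevant.

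The documents support three facts: the quality covariates are composites, they enter only at the second step, and recommendation-level pre-trial values are held monthly but unused. The documents do not support a firm size for the loss. The range runs from almost nothing at r near zero to somewhat over a quarter of the standard error at r = 0.7 with no other covariate. It is smaller once EQA is in the model, and smaller again for the rare reminder types. All of this rests on the assumed r, an ICC of 0.05, about 70 centres per arm and a normal approximation on the risk-difference scale.

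The change is worth making because the protocol itself foresees an effect below 10 points, and because it needs no new data collection.

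**What to change.** In the first resolution model and the first multilevel survival model, prespecify two fixed covariates and name the result as the main estimate:

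1. the EQA randomisation stratum;
2. the centre's pre-initiation level on the recommendation that matches the reminder type. This is either adherence in the month before initiation or, if it can be extracted from the same records, the prior-year resolution rate, which is closer to the outcome.

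State that all quality values, including EQA, EQPF and EQR in the later steps, are fixed before the trial starts.

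**Cost.** One merge from existing files and a short mapping from the ten reminders to the 25 recommendations, which the article does not give. In a logistic model, adjustment also changes the conditional odds ratio, so the gain appears as power or in a narrower marginal risk difference. That risk difference should be reported beside the odds ratio.

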### Data collection and management

The ICS primary care information system (SISAP) will be used to identify patients with a health status that could be improved by the health reminders, and execute a weekly update of patient status. The variables required to execute these algorithms will be obtained from the clinical registry of electronic health records. They include patient diagnoses (by CIE-10 code), primary care visits, clinical variables, drug prescriptions, and vaccinations. In addition to the variables specific to the intervention (resolution of the reminder), other explanatory and descriptive variables will be collected (Table 3). Data for the EQR (quality of data recording) will be collected from the SIDIAP database (*Sistema d’Informació per al Desenvolupament de la Investigació en Atenció Primària*) (Bolíbar et al. 2012). Moreover, the Medea socioeconomic index (Domínguez-Berjón et al. 2008). The EQA, EQPF (prescription quality standard), and other variables at the level of the professional or PCC will be obtained from the ICS information system.

**Table 3 Tab3:** Variables included in multi-level analysis

Variable	Explanation
Variables at the reminder level	
Type of clinical activity required^a^	Preventive or follow-up activities, immunizations, treatment initiation
Reminder generated	Yes or no
Clinical situation can be improved	Described in Table 1
Age and sex^a^	Older populations generate a higher number of clinical situations that can be improved because of the relationship between age and morbidities
Comorbidity, weighted according to CRG^a^	CRG (Clinical related groups) classify patients according to morbidity, based on diagnoses, status and severity in different categories. Each category has a morbidity weight. A priori, greater morbidity should generate a greater number of improvable clinical situations
Variables at the professional/PCC level	
Socioeconomic level of the PCC	Medea Index
Rurality	Construct based on size of municipality and population/Km^2^
Teaches family medicine	PCC or team member is accredited for postbaccalaureate training in Family and Community Medicine
Teaches basic nursing	PCC or team member is accredited for baccalaureate training in Nursing

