### Sample size

A 10 % difference between the proportion of resolved reminders and the assumed proportion in the intervention group of 59 % will be considered clinically relevant (Demakis et al. 2000). Assuming an alpha error of 0.01, 95 % power, and 10 % loss to follow-up, and correcting for an intraclass correlation in the PCCs of 0.05, each of the 4 study groups will require 15,950 reminders, a total of 63,800. The estimated number of reminders to be generated is shown in Table 1. Nonetheless, due to the design of the computerized tool, the need for cluster randomization, and the availability of the universal sample, it is not considered necessary to limit the study to the calculated sample size.

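### Comparing odds or hazard ratios across successive models cannot by itself show whether reminder-level variables change the intervention effect

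*Protocol article*

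**What the plan says.** Under Resolution of the reminder, at the reminder level, the protocol article states: "Multilevel logistic regression models will be fitted". Three steps follow:

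1. "The analytical strategy will be to estimate the intervention effect, taking into consideration the randomized professionals".
2. Professional-level quality is added: "next, the effect size will be estimated by introducing the quality variables from the professional level (EQPF, EQA, and EQR").
3. "Finally, we will determine whether introducing variables from the reminder level changes the intervention effect".

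Under Time to resolution of the improvable clinical situation the same sequence is applied to multilevel survival models, again to "then determine whether the variables at the reminder level change the estimated intervention effect".

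Table 3 lists the reminder-level variables. They include "Type of clinical activity required", age and sex, and weighted comorbidity. The Sample size section states clinical relevance as a 10% difference in the proportion resolved, with 59% assumed in the intervention group. The Randomization section allocates centres at random, stratified by quintile of the quality index.

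**The concern.** The last step asks whether the intervention effect changes when reminder-level variables enter. The natural output of a logistic model is an odds ratio and that of a survival model usually a hazard ratio. Neither is collapsible: the ratio within levels of a prognostic variable differs from the ratio ignoring that variable, even when the variable has the same distribution in every arm. A multilevel logistic model adds a scale effect, because its lowest-level variance is fixed and the coefficients and higher-level variances rescale as predictors enter.

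Centres are randomised, so no systematic case-mix confounding is expected. A ratio that moves between steps 1 and 3 may therefore reflect only the change of scale. It could be mistaken for case-mix imbalance, for effect modification, or for a larger adjusted effect. The successive models could also give different ratios for one effect, none on the scale on which the trial defines clinical relevance.

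**Working it through.** **Inputs from the article.** The Table 1 counts sum to 1,620,643. Smoking is 711,392 of these, a weight w = 0.439; blood pressure is 534,702, or 33.0%. The relevant difference is 10 points, with 59% in the intervention group, read here as 49% against 59%. The intraclass correlation is 0.05.

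**Assumed.** The article gives no resolution rates by reminder type and no predictor strengths. Table 2 makes reminder type a plausible strong predictor, since resolution ranges from an active prescription to a last record of non-smoker. Control rates are varied below for smoking against all other types. Case mix is identical in both arms, and the effect is one common odds ratio across types, so there is no confounding and no effect modification on the model's own scale.

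**Reference odds ratio.** For 49% against 59%: (0.59/0.41) / (0.49/0.51) = 1.498.

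**One case by hand: control 20% smoking, 70% other.** Intervention rates of 30% and 80% give the same odds ratio in both strata:
- Smoking: (0.30/0.70) / (0.20/0.80) = 1.714.
- Other: (0.80/0.20) / (0.70/0.30) = 1.714.
- Pooled control: 0.439 × 0.20 + 0.561 × 0.70 = 0.4805. Pooled intervention: 0.5805.
- Pooled odds ratio: (0.5805/0.4195) / (0.4805/0.5195) = 1.496.
- Log odds ratio: ln 1.714 / ln 1.496 = 0.539 / 0.403 = 1.34, a rise of 34%.
- Risk difference: 10 points in each stratum and 10 points pooled, so unchanged.

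**Other assumed rates.** Solve for b in w·expit(logit r₁ + b) + (1 − w)·expit(logit r₂ + b) = p₀ + 0.10, where r₁ and r₂ are the control rates and p₀ their weighted mean.

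| Control rate, smoking / other | OR without type | OR with type | Change in log OR |
|---|---|---|---|
| 40% / 55% | 1.50 | 1.51 | +2% |
| 30% / 60% | 1.50 | 1.56 | +10% |
| 20% / 70% | 1.50 | 1.71 | +34% |
| 10% / 60% | 1.51 | 1.78 | +41% |

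If the overall rates are held at exactly 49% and 59%, control smoking resolution of 35% gives 1.54 and 25% gives 1.64. A sharper contrast (15% smoking, 75.6% other) gives 1.90, so the upper end depends on the assumption.

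**Does a centre random intercept remove it?** No. Repeating the last three rows of the table within centre, with a latent-scale intraclass correlation of 0.05, gives +10%, +35% and +42%.

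**A general balanced covariate, 49% against 59%.** For a normal covariate with log-odds standard deviation 0.25, 0.5, 1.0 and 2.0, the odds ratio moves from 1.498 to 1.507, 1.534, 1.629 and 1.946. The log odds ratio rises by 1.5%, 5.9%, 20.9% and 64.8%.

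**Smaller effect.** With the 4.2-point improvement cited in the Background, 20%/70% gives 1.18 to 1.25 and 30%/60% gives 1.18 to 1.20. The relative shift in log odds ratio is nearly the same (+33% and +10%), but the absolute shift is smaller.

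**No effect.** The odds ratio stays at 1.00 whatever is added.

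No figure was computed for the hazard ratio. The argument there is qualitative.

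**The case against.** Several points on the other side stand.

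- **Type-specific models.** The Abstract describes an analysis of adherence for each type of reminder. Within such a model reminder type is constant and cannot shift the ratio. A pooled model is still the better reading of the quoted step, because Table 3 lists type of activity as a covariate and analysis by type is named separately as a subgroup analysis. The text is nevertheless ambiguous.
- **Weak predictors.** In type-specific models mainly age, sex and comorbidity remain, and their strength is unknown. If every model carries a patient random intercept, which the Statistical analysis section makes plausible, they shift the ratio much less.
- **No ratio is named.** The article speaks only of an effect or effect size, and a logistic model can also yield proportions. The problem arises only if the comparison is read from the ratios. A condensed article may leave the summary measure to the full plan, so its absence is not the point here. The point is that the stated comparison misleads on the models' natural scale.

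A reader might infer that any real effect is bound to be declared changed. The article does not support that. It states no threshold and no test for a change, so no rate of false declarations can be attached to the plan, and with weak predictors the shift is negligible. A reader might also infer that the trial's main result is compromised. It is not: the first model's estimate and the test of no effect do not depend on this comparison.

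**Conclusion.** The concern holds in limited form. The last step of both analysis sections is a stated comparison, and on the odds-ratio or hazard-ratio scale it cannot separate a change of scale from confounding or effect modification. Three conditions are needed: a true effect, a prognostic variable among those added, and a judgement made on the ratio. Under them, adding reminder type to a pooled model could move an odds ratio of about 1.50 to anywhere between about 1.51 and 1.78 over assumed smoking/other control rates from 40%/55% to 10%/60%. For predictors with a log-odds standard deviation of 0.5 or below, the log odds ratio moves by about 6% or less. The consequence is a possible misreading of a supplementary step, not an invalid trial result.

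**What to change.** Keep every planned model and judge the change on a collapsible scale. In Resolution of the reminder, report from each successive model the standardised difference in the proportion resolved at 12 months. In the time-to-resolution section, report the standardised difference in cumulative resolution at 12 months. Give both with intervals that respect clustering by centre. Robust or delta-method intervals suffice; resampling centres is an option if feasible, but with about 1.6 million expected reminders it should not be required.

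Add one sentence stating that a shift in the odds or hazard ratio between models is not by itself evidence of confounding or of a changed effect. This also puts the result on the scale of the 10-point difference in the Sample size section.

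The cost is wording, a post-estimation step on models already planned, and some computing time.

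### The first effect model omits the EQA quintile used to stratify randomisation, and an undefined "Reminder generated" flag sits among the variables later adjusted for

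*Protocol article*

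**What the plan says.** - **Protocol article, Randomization:** "centres will be stratified by the quintiles of EQA results in the month prior to study initiation". The stratum is therefore a PCC-level baseline value with a stated date.
- **Resolution of the reminder, reminder level:** multilevel logistic models are used so as to "introduce variables from different levels as adjustment variables in estimating the intervention effect". Three steps follow. Step 1 is to "estimate the intervention effect, taking into consideration the randomized professionals". Step 2 re-estimates the effect with EQPF, EQA and EQR added from the professional level. In step 3, "we will determine whether introducing variables from the reminder level changes the intervention effect".
- **Time to resolution of the improvable clinical situation:** the same three steps apply, and step 1 is called the initial model.
- **Data collection and management, Table 3:** the title is "Variables included in multi-level analysis". The reminder-level block contains type of activity, "Reminder generated" (yes or no, with no further definition), whether the situation can be improved, age and sex, and comorbidity. The visit variables are dated to the year before the study. EQA, EQPF and EQR carry no date.
- **Background:** EQA results are updated monthly, and the reminders are "related to 25 of the 62 recommendations considered as quality indicators in the EQA".

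**The concern.** There are two separate matters.

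First, stratified allocation balances the arms on EQA, so the difference between arms varies less than it would under simple randomisation. A model without the stratum does not recognise this. It leaves the variation between strata in the error term and reports too large a standard error. The EQA term at step 2 is not a clear substitute: it is a professional-level variable of unstated date, not the PCC quintile used for allocation.

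Second, a covariate that is a consequence of allocation should not be adjusted for when estimating the effect of allocation. Under Intervention groups, a generated reminder is what triggers the pop-up, and the control group receives feedback without reminders. Read that way, the flag would carry the effect that the model is meant to estimate. The document does not define it for control records, so the plan does not settle whether step 3 is harmless or removes the effect.

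**Working it through.** **The plan's own figures.** The protocol gives no figure on this point. Its one computed figure, 15,950 reminders per group, can be matched only by assuming an unstated cluster size: with 300 reminders per PCC, 902 × 15.95 / 0.9 = 15,985. Nothing below depends on it.

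**A. Omitted stratum**

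Inputs from the protocol:
- resolution 59%, and 49% after a 10-point difference (direction assumed)
- ICC 0.05
- 282 teams in 4 groups, so about 70 PCCs per arm
- analysis level 5%
- 4.2 points, the literature estimate given in the Background

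Assumed, because the document gives no figure: R², the share of between-PCC variance explained by the EQA quintile, taken as 10–30%.

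Table 1 sums to 1,620,643 expected reminders, or about 5,747 per PCC. The within-PCC part of the variance is then 0.95 / (0.05 × 5,747) = 0.3% of the between-PCC part and can be ignored.

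1. Reported SE without the stratum: √[0.05 × (0.59×0.41 + 0.49×0.51) / 70] = 1.87 points.
2. SE with the stratum: 1.87 × √(1 − R²). This is also the true SD of the estimate under stratified allocation.
3. True type I error of the unadjusted test: 2 × [1 − Φ(1.96 / √(1 − R²))].
4. Power at 4.2 points, unadjusted: Φ[(4.2 − 1.96 × 1.87) / (1.87√(1 − R²))]. Adjusted: Φ[4.2 / (1.87√(1 − R²)) − 1.96].

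| R² | SE with stratum | Reduction in SE | Type I error, unadjusted | Power, unadjusted | Power, adjusted |
|---|---|---|---|---|---|
| 0 | 1.87 | 0% | 5.0% | 61% | 61% |
| 0.1 | 1.77 | 5% | 3.9% | 62% | 66% |
| 0.3 | 1.57 (1.565) | 16% | 1.9% | 63% | 77% |

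A simulation of PCC-level regressions with 70 PCCs per arm gives the same picture. At R² = 0.2 the type I error is 2.5% unadjusted and 4.7% adjusted, and power for an assumed 3-point effect is 32% and 42%.

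At the design difference, Φ(10/1.87 − 1.96) exceeds 0.999 without any adjustment.

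The gain is smaller for rare reminder types. For the rarest in Table 1, 11,394 / 282 is about 40 per PCC, and the within-PCC part is 0.95 / (0.05 × 40.4) = 0.47 of the between-PCC part. At R² = 0.3 the SE then falls by 1 − √(1 − 0.3/1.47) = 11%.

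**B. The undefined flag**

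Logistic models were fitted to simulated records (59% versus 49%), with arm and flag entered together:

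| Meaning of the flag | Arm OR without flag | Arm OR with flag |
|---|---|---|
| Yes in all intervention records, no in control | 1.53 | not estimable (rank 2 of 3) |
| Yes in 80–95% of intervention records, never in control, effect only through the reminder | 1.37–1.50 | 0.98–1.04 |
| Yes in every record of both arms | 1.50 | the flag is a constant and drops out |
| Yes in 90% of each arm | 1.45 | 1.45 |

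Under none of these meanings does the flag improve the estimate.

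**The case against.** **The stratum costs precision only, and EQA enters in the next model.** This stands as far as bias goes. A reader might infer that the first comparison is biased; it is not, because omitting a balanced stratum only makes the test conservative. The size also depends on an assumed R² and on an effect well below 10 points. The Discussion does say that the established feedback may lead to a smaller effect.

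**The flag may be harmless.** A reader might infer that it is the intervention itself and perfectly aligned with arm. The documents do not support that as fact: the variable is never defined for control records, and Sample size counts reminders in all four groups, so a reminder can also mean a record flagged by the algorithm and not shown. Table 3 has no row for trial arm, so the flag could even be the exposure term, and the surrounding text calls the collected variables explanatory and descriptive. The step 3 text does not name it. All of this stands. What remains is that the table of model variables places it in the block to be introduced, and that it serves no purpose as an adjuster on any of these readings.

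**Timing of EQA is a detail for the analysis plan.** This largely stands. Nothing says that in-trial values will be used. The risk that EQA would be partly the outcome is conditional on that choice.

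**One might say that no estimate is named as the result.** That goes too far: the survival section calls step 1 the initial model, and step 3 is framed as a check. Only step 2 is worded as a further effect estimate.

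**Conclusion.** The point holds in a limited form. The first model leaves out the factor by which PCCs were stratified, and no step names the randomised quintile. The consequence is a conservative first test. With R² of 10–30% (assumed), about 70 PCCs per arm, ICC 0.05 and many reminders per PCC, the SE would be 5–16% lower with the stratum included, and power at 4.2 points would rise by about 4 to 13 percentage points. It makes no practical difference at 10 points and none if EQA does not predict resolution.

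On the flag, the supportable statement is conditional. If it records that a reminder was shown, step 3 removes the arm effect or cannot estimate it; if it is an algorithm flag common to all arms, it is constant or uninformative. The document does not decide between these. A change in the odds ratio at steps 2 or 3 should in any case be read with care, because odds ratios can shift when prognostic covariates are added even under sound randomisation; the size of that shift has not been worked out here.

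**What to change.** 1. In the first model for resolution and the first model for time to resolution, include the EQA quintile as randomised alongside arm and the hierarchical random effects, and name these as the primary models.
2. Label steps 2 and 3 as sensitivity analyses, and state that EQA, EQPF and EQR are pre-study values.
3. Define "Reminder generated" for the control group and keep it out of the adjustment covariates. If it is collected to describe delivery of the intervention, report it descriptively.

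The cost is wording only. The EQA quintile is already needed for randomisation, the other variables are already to be collected, and the sample size does not change.
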